We will use a series of tests and tasks to validate the VSCT. We hypothesize a positive correlation between the VSCT and SCT, as both are designed to measure the same construct—namely, the ability to form cognitive maps. We also hypothesize a positive correlation between the VSCT and Backward Corsi, as working memory is a key component in the formation and maintenance of cognitive maps (
Epstein *et al.*, 2017). Conversely, we do not expect a significant correlation between the VSCT and RAVLT. We included the Rey Auditory Verbal Learning Test (RAVLT) in our study precisely to assess discriminant validity. The RAVLT measures verbal episodic memory, while the VSCT targets visuospatial configuration memory—two constructs that are theoretically and empirically distinct (
Suri *et al.*, 2017). By including the RAVLT and confirming that it does not significantly correlate with performance on the VSCT, we provide evidence that the VSCT is not simply capturing general memory ability, but rather a more specific visuospatial memory component. This lack of correlation supports the discriminant validity of our task, helping to confirm that it measures a construct different from that assessed by standard verbal memory tasks.

Finally, to evaluate VSCT feasibility we will use the Simulator Sickness Questionnaire (SSQ) (
Kennedy *et al*., 1993).

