### Participants

As the study aims to evaluate
**convergent and discriminant validity** of VSCT, by comparing VSCT correlation with SCT to the correlation of RAVLT with SCT, an
*a priori* power analysis was conducted using

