**G*Power 3.1**
Faul *et al.* (2009). Assuming a
**moderate to large effect size (Cohen’s q = 0.4)**, a significance level of
**α = 0.05**, and a desired power of
**0.95**, The required sample size for comparing two independent correlation coefficients using a z-test for dependent Pearson’s r was calculated as 166
**participants**. Taken this for granted, and bearing in mind that the data to correlate are not yielded with a paper-and-pencil questionnaire- but a virtual setting requiring training and adaptation, we weight the effect size indication with previous research using similar aims and methods.

This was the case in
da Costa *et al.* (2022), who validated two immersive virtual reality tasks for spatial orientation using correlational and group comparison analyses. The authors reported significant associations between the virtual tasks and traditional cognitive measures, as well as successful group discrimination.

The participants represented a sample size large enough to yield statistically reliable confidence intervals. It should be noted that the study employed a between-subjects design; however, participants from the two groups were combined. In contrast, our study will correlate the two groups with two different variables.

Furthermore,
*
He *et al.* (2022)
* employed a fully within-subjects design to validate a spatial perspective-taking task in ambulatory virtual reality, using a sample size comparable to ours. However, since within-subjects designs typically offer greater statistical power, we acknowledge that our between-subjects design may require a larger sample to achieve equivalent sensitivity. We have accounted for this by adopting a conservative effect size estimate and grounding our decision in the specific demands of VR-based testing, which introduces variability due to training and adaptation phases.

Participants will be actively recruited to participate in the intervention across various University of Bologna Campus locations. Recruitment will be facilitated through targeted advertisements and consecutive enrollment procedures to ensure diverse participant representation and data robustness. 

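### Non-significance of the VSCT–RAVLT correlation is taken as evidence of discriminant validity; it does not show the correlation is small, and the described design gives no participant both tests

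*Protocol article*

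**What the plan says.** In the Introduction (Validation of a new 3D spatial task), the protocol article says the RAVLT is included to assess discriminant validity and that "we do not expect a significant correlation between the VSCT and RAVLT". It then turns this expectation into an inference: by "confirming that it does not significantly correlate with performance on the VSCT, we provide evidence" that the VSCT is not merely capturing general memory, and "This lack of correlation supports the discriminant validity of our task". No largest acceptable correlation, confidence limit or reliability condition goes with the rule.

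Other sections bear on it:

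- **Participants** gives a different basis for convergent and discriminant validity, "by comparing VSCT correlation with SCT to the correlation of RAVLT with SCT". The sample size is built on that comparison with a "moderate to large effect size (Cohen’s q = 0.4").
- **Procedure** gives the VSCT to the experimental (VR) group and the RAVLT to the control (AV) group. The Introduction calls the design between-subjects.
- **Correlation analysis** lists a matrix of Corsi, SBSOD, VSCT and SCT. The RAVLT is not in it. Split-half or alpha reliability and a test–retest subsample are planned, but neither is tied to the reading of the null result.

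**The concern.** Failing to reject a zero correlation is treated as showing that the correlation is absent. The same result arises when the true correlation is modest and the sample cannot detect it, or when measurement error in the VSCT shrinks an overlap that is there. The second route has a perverse effect: taken alone, the rule is easier to pass the less reliable the new instrument is. The study could then state that the VSCT is distinct from verbal memory on data compatible with a sizeable overlap.

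There is a prior problem. A correlation needs both scores on the same people, and the Procedure does not provide them.

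**Working it through.** **Inputs.** Cohen's q = 0.4, alpha 0.05, power 0.95 and the figure 166 come from Participants. Assumptions: two-sided testing, 1:1 allocation, bivariate normality and, for the reliability check only, a RAVLT reliability of 0.8. The article does not say whether 166 is per group or in total, so both readings are shown.

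**1. The plan's own figure.** For two independent correlations, n per group = 2 × ((z_alpha + z_power)/q)² + 3 = 2 × ((1.960 + 1.645)/0.4)² + 3 = 165.4, hence 166. The stated inputs therefore reproduce 166 as a per-group number (332 in total). The text describes the test both as "0.95, The required sample size for comparing two independent correlation coefficients" and as a "z-test for dependent Pearson’s r was calculated as 166". On either reading, q is a difference between two correlations; it puts no limit on VSCT–RAVLT.

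**2. Chance of passing the rule.** With Fisher's z, P(non-significant) = Φ(1.96 − m) − Φ(−1.96 − m), where m = atanh(r) × √(n − 3) and n is the number of people with both scores. For r = 0.20, atanh(r) = 0.2027. At n = 83, m = 0.2027 × √80 = 1.81, giving 56%. At n = 166, m = 0.2027 × √163 = 2.59, giving 27%.

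| True r | n = 83 | n = 166 |
|---|---|---|
| 0 (includes a pure-noise VSCT) | 95% | 95% |
| 0.15 | 73% | 51% |
| 0.20 | 56% | 27% |
| 0.25 | 37% | 10% |
| 0.30 | 21% | 2% |
| 0.40 | 3% | <0.1% |

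The largest observed |r| that stays non-significant is tanh(1.96/√(n − 3)): 0.216 at n = 83 and 0.152 at n = 166. At n = 83 an observed r of 0.21 would count as support, with a 95% confidence interval of −0.01 to 0.41.

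**3. Effect of VSCT reliability.** Observed r = true-score r × √(VSCT reliability × RAVLT reliability). With a true-score r of 0.30:

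| VSCT reliability (assumed) | Observed r | Passes, n = 83 | Passes, n = 166 |
|---|---|---|---|
| 0.8 | 0.24 | 41% | 12% |
| 0.5 | 0.19 | 60% | 31% |
| 0.3 | 0.147 | 74% | 53% |

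**4. Can it be computed?** The Introduction needs pairs of VSCT and RAVLT scores. The Procedure gives the VSCT to one group and the RAVLT to the other, and the Participants section says the two groups will be correlated with two different variables. The number of pairs is therefore zero as described, and steps 2 and 3 show what the rule would do if pairs existed. The contrast under Participants can be run, because both groups take the SCT.

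**5. Would a ±0.30 bound do better?** ±0.30 is an illustrative bound, not one from the article. Requiring the 90% interval to lie inside it allows an observed |r| up to tanh(atanh(0.30) − 1.645/√(n − 3)): 0.125 at n = 83, stricter than 0.216, but 0.179 at n = 166, more lenient than 0.152. If the true r is 0, the criterion is met 74% and 98% of the time.

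**The case against.** The strongest reply is that the criticised sentences are rationale in the Introduction. The basis for discriminant validity under Participants is a formal contrast of two correlations, and the study is sized for it. This stands in part: a runnable contrast is already named. But it compares VSCT–SCT with RAVLT–SCT and says nothing about the size of VSCT–RAVLT, and the Introduction still states its own inference without condition.

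The second reply is that a noisy VSCT would not get through the whole programme. Positive correlations with the SCT and the backward Corsi are also expected, and reliability will be estimated. This stands too. A reader might infer that an unreliable VSCT would end up validated; the article does not support that. What remains is that the discriminant claim is not made conditional on those results.

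Third, a reader might infer that a moderate correlation would often slip through. The figures do not bear that out: a true r of 0.30 passes about one time in five at 83 and about one time in fifty at 166. Frequent passing is confined to correlations of roughly 0.15 to 0.20, plus 0.25 at the smaller size, unless reliability is poor. The size of 83 is itself an assumption.

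Finally, the Materials section introduces the SCT and RAVLT as tasks measuring each participant's performance, which could be read as everyone taking the RAVLT. The Procedure says otherwise. That is a reason to reconcile the sections, not evidence that paired scores will exist.

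**Conclusion.** The point holds in a limited form. The Introduction fixes an invalid inference, and no other section attaches a bound, interval or reliability condition to it. If paired scores existed, a true correlation of 0.20 would be read as support 56% of the time with 83 people and 27% with 166; for 0.30 the figures are 21% and 2%. They rest on two-sided alpha 0.05 and normality, and the 83 also on reading 166 as a total split 1:1. As the design is described there are no paired scores, so the correlation cannot be computed; the Introduction, Participants, Procedure and Correlation analysis sections must be reconciled. The sponsor should make the change: left as it is, the rule can yield an unsupported statement about what the VSCT measures.

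**What to change.** 1. Delete the statement that a non-significant VSCT–RAVLT correlation supports discriminant validity, and reconcile the four sections on who takes which test and which correlations are compared.
2. If the groups stay separate, base the claim on the contrast named under Participants: VSCT–SCT in the VR group against RAVLT–SCT in the AV group, by Fisher's z for independent correlations, using the first SCT administration. Report the difference with its 95% confidence interval, read it alongside the planned VSCT reliability, and state that it does not bound the VSCT–RAVLT overlap.
3. Only if the design does give both tests to the same people, make a VSCT–RAVLT claim. Require the confidence interval to lie inside a pre-stated bound, together with a dependent-correlation test that VSCT–SCT exceeds VSCT–RAVLT. Choose the bound for the actual n, since ±0.30 is tighter than the present rule at 83 but looser at 166.

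**Cost.** Items 1 and 2 change the analysis rule and the text and need no new data, but the claim becomes narrower. On the Fisher z scale the 95% half-width of the contrast is 1.96 × √(2/(n − 3)): 0.31 with 83 per group and 0.22 with 166 per group. Item 3 is more than wording if the tests are now split between groups: it means giving both tests to the same people, and the claim becomes harder to make. With a ±0.30 bound and a true r of 0, 93 people with both scores are needed for 80% power and 139 for 95%.

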## Methods

### Open science commitment

Our protocol is available on the Open Science Network, and our data will be made accessible in the near future (
https://osf.io/3dmsy/).

### Participants

As the study aims to evaluate
**convergent and discriminant validity** of VSCT, by comparing VSCT correlation with SCT to the correlation of RAVLT with SCT, an
*a priori* power analysis was conducted using
**G*Power 3.1**
Faul *et al.* (2009). Assuming a
**moderate to large effect size (Cohen’s q = 0.4)**, a significance level of
**α = 0.05**, and a desired power of
**0.95**, The required sample size for comparing two independent correlation coefficients using a z-test for dependent Pearson’s r was calculated as 166
**participants**. Taken this for granted, and bearing in mind that the data to correlate are not yielded with a paper-and-pencil questionnaire- but a virtual setting requiring training and adaptation, we weight the effect size indication with previous research using similar aims and methods.

This was the case in
da Costa *et al.* (2022), who validated two immersive virtual reality tasks for spatial orientation using correlational and group comparison analyses. The authors reported significant associations between the virtual tasks and traditional cognitive measures, as well as successful group discrimination.

The participants represented a sample size large enough to yield statistically reliable confidence intervals. It should be noted that the study employed a between-subjects design; however, participants from the two groups were combined. In contrast, our study will correlate the two groups with two different variables.

Furthermore,
*
He *et al.* (2022)
* employed a fully within-subjects design to validate a spatial perspective-taking task in ambulatory virtual reality, using a sample size comparable to ours. However, since within-subjects designs typically offer greater statistical power, we acknowledge that our between-subjects design may require a larger sample to achieve equivalent sensitivity. We have accounted for this by adopting a conservative effect size estimate and grounding our decision in the specific demands of VR-based testing, which introduces variability due to training and adaptation phases.

Participants will be actively recruited to participate in the intervention across various University of Bologna Campus locations. Recruitment will be facilitated through targeted advertisements and consecutive enrollment procedures to ensure diverse participant representation and data robustness. 

The project will be advertised in public spaces and social platforms. Participants will be invited to make an appointment with the researchers by e-mail after the first evaluation phase. During this initial contact, the researchers will explain the purpose of the study, answer any follow-up questions, and invite participants to come to the Department of Psychology. Upon arrival at the lab, participants will be asked to sign an informed consent form and compile the personal data processing form. No identifying personal information (e.g., names, contact details, or video recordings) will be collected or stored. Participants are identified only by randomized numeric codes, and all reported results will be presented at the group level, ensuring that no individual can be identified in any publication or presentation of the data.

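### The sample size of 166 is the per-group number for comparing two independent correlations; as a study total it gives about 72% power, not 95%

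*Protocol article*

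**What the plan says.** The Participants section bases the sample size on convergent and discriminant validity, assessed "by comparing VSCT correlation with SCT to the correlation of RAVLT with SCT, an" a priori power analysis following from that aim. The inputs are a "moderate to large effect size (Cohen’s q = 0.4), a significance level of" 0.05 and a desired power of 0.95. The result reads: "The required sample size for comparing two independent correlation coefficients using a z-test for dependent Pearson’s r was calculated as 166" participants. No other total, per-group number, allocation ratio or allowance for loss is given.

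The same section contrasts the design with an earlier validation study that pooled its groups: "our study will correlate the two groups with two different variables". It concedes that a between-subjects design may need more participants than a within-subjects one, and then says: "We have accounted for this by adopting a conservative effect size estimate".

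The Introduction (Validation of a new 3D spatial task) and the Procedure confirm that each participant joins one of two groups. The VR group does the VSCT and the AV group does the RAVLT. Both groups do the SCT.

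**The concern.** The two correlations to be compared come from different people, so the test is one for two independent samples. Its sample size formula returns a number for each group. The protocol reports that number as the required number of participants, without saying that it applies to each group.

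The sentence also names two incompatible tests, since the coefficients are called independent and the z-test is called one for dependent correlations.

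The remark about a conservative effect size does not help. The same section calls q = 0.4 moderate to large, and assuming a larger effect lowers the required n.

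This is the only power statement in the document. If 166 people are recruited, a non-significant difference between the two correlations would be read as coming from a study with 95% power. The actual risk of missing q = 0.4 would be more than five times the stated 5%.

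**Working it through.** **Inputs.** From Participants: q = 0.4 (a difference of Fisher z values), alpha 0.05, power 0.95, stated size 166. From the Introduction and Procedure: two separate groups. Assumed because not stated: 1:1 allocation, no loss, and a two-sided test.

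**Reproducing 166.** For two independent correlations with equal groups,

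n per group = 2 × ((z for alpha + z for power) / q)² + 3.

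- Two-sided: 2 × ((1.960 + 1.645) / 0.4)² + 3 = 165.4, so **166 per group, 332 in total**.
- One-sided: 138.3, so 139 per group, 278 in total.

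The stated figure is thus the two-sided per-group number exactly. Neither version gives 166 as a total at 95% power. As 166 equals the unadjusted result, no increase for the design is visible in it.

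**Power with 166 in total (83 per group).** The standard error of the difference is √(1/80 + 1/80) = √(2/80) = 0.158.

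| Quantity | Calculation | Result |
|---|---|---|
| Power at q = 0.4, two-sided | Φ(0.4/0.158 − 1.960) = Φ(0.570) | 71.6% |
| Power at q = 0.4, one-sided | Φ(0.4/0.158 − 1.645) | 81.2% |
| Power at q = 0.3, two-sided | Φ(0.3/0.158 − 1.960) | 47.5% |
| q detectable with 95% power | 3.605 × 0.158 | 0.57 |
| q detectable with 80% power | (1.960 + 0.842) × 0.158 | 0.44 |

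Simulation with 83 per group gave 72%. With 166 per group the formula gives 95.1%. Unequal splits of 166 do worse: 66/100 gives 69.6% and 55/111 gives 65.9%.

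**Other routes to 166.**

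- A single correlation tested against zero, with Fisher z of 0.4, needs 71 (one-sided) or 85 (two-sided).
- One-sided testing at 80% power needs 81 per group, 162 in total. This is close to 166 but contradicts the stated power of 0.95.
- A test of dependent correlations sharing the SCT needs roughly 153 to 182 people in all, two-sided, if the VSCT–RAVLT correlation is assumed to be 0 to 0.1 and the RAVLT–SCT correlation 0 to 0.3. One assumed combination gives exactly 166. This requires every participant to do VSCT, RAVLT and SCT, which the design excludes. The document states none of the correlations that such a calculation needs.

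**The case against.** The strongest objection is that the text says neither in total nor per group. An exact match to the per-group formula fits a dropped label as well as an underpowered study, and if 166 per group was meant, power is 95.1%. This stands as a limit on the 72% figure, which depends on reading 166 as the total. It does not clear the sentence: without a qualifier the plain reading is the total, and on the other reading the protocol understates recruitment by half.

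A second objection is that the Plan of analysis lists t-tests, a correlation matrix and reliability, but no test of a difference between correlations. For a single correlation with 83 people in the VR group, two-sided Fisher z power is about 97% at r = 0.4, 90% at r = 0.35 and 79% at r = 0.3. This is fair and confines the loss of power to the between-group comparison. But Participants names that comparison as the validity aim and attaches the 95% to it.

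A third is that the Hypotheses text speaks of a VSCT–RAVLT correlation, and Materials introduces the SCT and RAVLT as tasks for each participant, which might suggest dependent correlations. The Procedure and the two task-condition descriptions assign VSCT and RAVLT to different groups, so this reading fails.

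**Conclusion.** The concern holds. For the comparison that the protocol names, 166 is correct only as a per-group number, with 332 in total. Read as written, as the number of participants, it gives 71.6% power at q = 0.4 and a type II error of about 28%, and reaches 95% power only at q = 0.57. This rests on a two-sided test, which is the only sidedness that reproduces 166 at 95% power, on equal allocation and on no loss. Unequal groups or loss would lower power further. A one-sided test would raise it to 81.2%, still short of 95%.

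The independent/dependent wording is a separate internal contradiction, and the claim that the effect size is conservative conflicts with the section's own description of it.

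**What to change.** Correct the Participants section in one of two ways:

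- **If 166 is the total:** state that 166 participants (83 per group) give 72% power for q = 0.4 at two-sided alpha 0.05, and 95% power for q = 0.57.
- **If 166 per group was intended:** state 166 per group, 332 in total.

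In either case, state the sidedness and the allocation ratio, delete the word dependent while the comparison is between groups, and delete the claim that the effect size is conservative.

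The first option is a wording change that needs no extra participants, but the stated power becomes less favourable. The second keeps 95% power and, if only 166 were planned in all, doubles recruitment.

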*Procedure*
**

 Participants will be assigned in a pseudo-randomized single-blinded manner to one of the two groups (Auditory Verbal (AV) vs. Virtual Reality (VR)). Both groups will be asked to perform an initial assessment of their spatial abilities using the 40-item version of SCT. In the next phase, the experimental group will be made to wear the "HTC VIVE" visor that will allow them to perform the Virtual Spatial Configuration Task in VR (VR condition); the control group will be administered the auditory verbal memory task (AV condition). Both groups will be given the SCT again at the end of the task (See
Figure 2). 

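### The sample size is said to rest on a conservative effect size that covers the between-subjects design and VR variability, but 166 is exactly the unadjusted result for q = 0.4 and no further allowance is shown

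*Protocol article*

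**What the plan says.** All the sizing text is in the protocol article, Methods, Participants.

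- The effect size is a "moderate to large effect size (Cohen’s q = 0.4", with alpha 0.05 and power 0.95.
- The result is given as: "The required sample size for comparing two independent correlation coefficients using a z-test for dependent Pearson’s r was calculated as 166" participants.
- After that number, the article says "we weight the effect size indication with previous research using similar aims and methods" and describes two earlier VR validation studies. It quotes no effect size from either.
- It notes that one of those studies was fully within-subjects with a similar sample size, and adds: "we acknowledge that our between-subjects design may require a larger sample to achieve equivalent sensitivity".
- It closes the matter with: "We have accounted for this by adopting a conservative effect size estimate and grounding our decision in the specific demands of VR-based testing". The rest of that sentence refers to variability from the training and adaptation phases.

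The Procedure section confirms two separate arms, with participants assigned "to one of the two groups (Auditory Verbal (AV) vs. Virtual Reality (VR". The Participants section says each group will be correlated with a different variable, so the two correlations to be compared come from different people.

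**The concern.** In sample-size work, a conservative effect size is one set below the effect that is expected, so that the study keeps its power if the expectation proves optimistic. The article names a sensitivity problem, says it was handled in this way, and gives no second value of q, no revised number and no inflation factor. The number printed before the discussion of earlier studies is the only one printed after it.

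The comparison of the VSCT–SCT correlation with the RAVLT–SCT correlation is the stated basis for sizing the study. A reader who accepts the sentence will believe that the 95% power already includes a reserve for a smaller effect or for noisier VR scores. If it does not, the study has its stated power only at q = 0.4 or above, and only if 166 is the number per group.

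**Working it through.** **Inputs.** From Participants: q = 0.4, alpha 0.05, power 0.95, stated N 166. From Procedure: two groups. Not stated, so assumed: two-sided testing and 1:1 allocation.

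**Step 1: reproduce 166.** For two independent correlations compared on the Fisher z scale,

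n per group = 2 × ((z for alpha + z for power) / q)² + 3 = 2 × ((1.960 + 1.645) / 0.4)² + 3 = 165.43, rounded up to **166 per group** (332 in total).

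The stated figure is therefore matched exactly, as a per-group number. Other readings of the same inputs do not give 166:

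- One-sided testing gives 139 per group, 278 in total.
- An approximate dependent-correlations variance, 2(1 − c)/(n − 3) with assumed c from 0.1 to 0.5, gives 150 down to 85 (two-sided).
- No variant tried at alpha 0.05 and power 0.95 gives 166 as a two-group total.

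**Step 2: is there a reserve in 166?** The smallest q detectable with 95% power is (1.960 + 1.645) × √(2/(n − 3)).

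- n = 166 per group: 3.605 × √(2/163) = 0.399
- n = 83 per group: 3.605 × √(2/80) = 0.570

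With 166 per group the detectable q equals the planning value to two decimals. Nothing has been added for a smaller effect.

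**Step 3: power when the true q is at or below 0.4.** Power = Φ(q / √(2/(n − 3)) − 1.960).

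| True q | 166 per group | 83 per group (166 in total) |
|---|---|---|
| 0.40 | 95.1% | 71.6% |
| 0.35 | 88.5% | 60.0% |
| 0.30 | 77.3% | 47.5% |

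For example, at q = 0.30 and 166 per group: 0.30/0.1108 − 1.960 = 0.748, and Φ(0.748) = 0.773.

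**The case against.** Four points on the other side deserve weight.

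**The two labels need not conflict.** A reader might infer that a moderate-to-large q cannot be conservative, so that the article contradicts itself and no safety margin exists. The documents do not support that. Moderate to large places q on a conventional scale; conservative compares it with what the authors expect. The Introduction argues that VSCT and SCT measure the same construct and that verbal memory is distinct. If the authors expected, say, r = 0.50 against 0 (an assumption for illustration), q would be 0.55 and 0.40 would indeed be cautious. What stands is narrower: the article gives no expected q and no source, so the reader cannot see that 0.4 is cautious.

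**The formula already carries the between-groups variance.** This is correct if 166 is per group, and it rules out saying that nothing was done for the between-subjects design on that reading. It does not rescue the sentence, which claims compensation through the effect size, and it does not touch VR variability. If 166 is the total, the between-groups variance is not covered.

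**VR noise need not push q below 0.4.** It is tempting to take 0.4 as an error-free value and reduce it for measurement error. The article does not say that 0.4 is error-free, and a planning q ordinarily refers to observed scores, so that reduction is not established here.

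**The lowest power figures come mainly from another ambiguity.** The values for 83 per group reflect uncertainty over whether 166 is per group or total, more than the word conservative. That is a separate matter. Both columns are shown because the text says 166 participants and either reading may be taken. On the per-group reading the loss is moderate: power stays at 80% or more down to q of about 0.31.

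The article is condensed, and a fuller protocol may hold the rationale. The point is still not an omission: the article makes a positive statement about its sizing that its own figures do not show.

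**Conclusion.** The concern holds in limited form. The article says that reduced sensitivity and VR variability were dealt with by a conservative effect size. Its only effect size is q = 0.4, and 166 is exactly the unadjusted per-group result for that value. No allowance beyond q = 0.4 is shown, and none is present in the number. It cannot be concluded that 0.4 is optimistic, or that the authors made no allowance in choosing it; only that the basis for calling it conservative is absent.

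The calculation itself is not wrong: 166 reproduces. The size of the issue depends on how 166 is read. Per group, the study has its stated power at q = 0.40 and falls short of it below that. As a total, it has about 72% rather than 95% even at the planning value. These figures rest on two-sided alpha 0.05, equal groups and the Fisher z approximation.

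**What to change.** In Participants:

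1. Either delete the sentence claiming a conservative effect size and that the problem has been accounted for, or keep it and state the expected q, with its source, that makes 0.4 conservative.
2. State whether 166 is the number per group or the total, together with the sidedness and allocation ratio.
3. Restate power for the actual group sizes. For 166 per group: 95%, 88% and 77% at q = 0.40, 0.35 and 0.30. For 83 per group: 72%, 60% and 48%, with 95% power only at q of about 0.57.

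The cost is a few sentences and a less favourable-looking power statement. This correction needs no extra participants.
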